***Exercise***

Subjects assigned to this arm will perform regular exercise at an energy cost of 12.5% of total daily energy needs measured at baseline by doubly labeled water, 24h-chamber and intake/balance requirements. The exercise regimen will consist of 5 days/wk. sessions of either walking/running or bicycling, or a combination (2 days). The energy cost of the exercise sessions will be calculated from the weekly desired energy cost divided by five. We have selected 5 rather than 7 days per wk. of exercise to comply with the American College of Sports Medicine (ACSM) recommendations of 3-5 days per wk. of aerobic exercise 126. Five days per wk. is thought to be the upper limit to minimize the risk of injury 127. Based on experience, we feel that the subjects’ compliance and enjoyment of the PA will be greater if they are allowed to choose from several modes of exercise.

The exercise prescription for each subject will be individually developed and assigned. Since the goal of the exercise session is simply to “utilize energy”, subjects will be allowed to choose a comfortable exercise intensity within the range recommended by the ACSM (i.e., 50-75% of maximum oxygen uptake or 60-85% of maximum heart rate)126. Briefly, the time subjects will need to walk, run or bicycle will be calculated from oxygen cost of activities measured in the exercise facility. Target heart rate will be the average heart rate measured during the steady-state measurement. Subjects will be instructed to exercise for the prescribed amount of time at an intensity that maintains a heart rate within 5 bpm of target heart rate measured via a portable heart rate monitor. Individual exercise prescriptions will be readjusted weekly for the 1st mo.; every 2 wks. for the next 2 mos.

Following the initial testing period, subjects randomized in the CR+PA arm will begin their exercise program (training phase) slowly (so as not to induce soreness or injury) and in coordination with the diet. The goal, however, is to have the subjects achieve their exercise prescription in its entirety by 6 wks. (Table 1). Subjects will exercise between 40 min. (jogging at 6.0mph) and 95 min. (walking at 3.5 mph) per session depending on the mode and intensity of the chosen exercise.

## Table 1

| **Week** | **Prescription** |
| --- | --- |
| 1 | 2 d/week for ½ calculated time |
| 2 and 3 | 4 d/week for ½ calculated time |
| 4 | 4 d/week for ¾ calculated time |
| 5 | 4 d/week for full time |
| 6 | 5 d/week for full time |

The PBRC Fitness staff will have frequent contact with thesubjects. During the 6-wk. training phase, subjects will perform all exercise at the PBRC Fitness Center, closely monitored by the fitness staff. After this progressive training phase, subjects will exercise at the PBRC 3 days per wk. and have the option of exercising on their own for the remaining 2 days. Since the terrain around Baton Rouge is flat, subjects will be allowed to walk or run outside, but will be required to bicycle indoors on a cycle ergometer due to a greater difficulty of controlling environmental factors (i.e., wind, traffic, and road surfaces). Exercise compliance will be strictly monitored with exercise logs, heart rate data and body wt. Subjects will also be monitored using accelerometers and doubly labeled water at different times. Thus, subjects may be asked to exercise more frequently at the Center if compliance to the program is in question.

## Timeline

During feeding phase (-.5 to 3 mo.). During the first 3.5 mos. of feeding at the Center, participants will meet as a group each week to discuss: a) basic concepts related to the participant’s, b) problems related to compliance and attendance that participants are experiencing, c) preparation for the self-selected diet period and exercise regimen (in 1 arm), and d) basic principles of lifestyle behavior modification. These groups will attempt to boost morale and motivation to comply with the feeding protocol and will provide psychoeducational material that prepares the participant for the next phase. Participants will be asked to fill out a daily food record during this period.

During Mo. 4-6. During the next 3 mos., participants will learn to modify eating behavior (and PA in 1 arm) while eating a self-selected diet (CR or CR+PA). During the previous phase, the concepts of lifestyle behavior modification will have been presented. During this phase, these concepts will be translated into action. The primary aims of this phase will be to: a) follow the prescribed dietary plan, b) follow the prescribed PA plan, c) eat 3 meals per day on a regular schedule, d) solve problems that cause sub-optimal compliance with the program, and e) manage emotions or other states (e.g., hunger) that cause sub-optimal compliance. To accomplish these objectives, participants will attend individual or group therapy sessions every 2 weeks. Participants will be asked to fill out a daily food record during this period.

Individual tailoring of treatment. One aspect of lifestyle behavior modification, i.e. frequent and regular therapeutic contact, has been found to be very important for long-term behavior change. To accomplish frequent contact, treatment will be tailored to the needs of the individual participant using internet-based contact and/or telephone contact. Also, for persons who are having difficulty following the prescribed dietary or PA program, the intervention will be tailored to address the unique problems of the individual. The rate of predicted weight loss will be calculated using a 2-reservoir dynamic model of the energy balance equation as described by Alpert 128. This data will be used to monitor compliance and will not be shared with the volunteer. Metabolic weight will be measured once per week. Participants who fail to meet 60% of the expected rate of wt. loss will be interviewed very carefully to identify reasons for potential sup-optimal compliance with the prescribed treatment. Compliance will also be assessed by measures of metabolic rate, heart rate monitors, accelerometers and doubly labeled water. If problems related to compliance are identified, solutions to the problem will be established and individualized interventions will be initiated and tested for specified periods of time. If these interventions result in hypothesized changes in weight, they will be continued; if not, new strategies will be formulated and tested until success is achieved. Only after different tries, subjects will be asked to leave the study.

## Outcome measures

**Primary outcome**. The primary endpoint will be the rate of energy expenditure under resting, sedentary and free living conditions. Each component will be assessed by state-of-the-art methods (ventilated hood, respiratory chamber and doubly labeled water). Sedentary energy expenditure in the respiratory chamber has been used for the power analysis. The reason is that this method is the most sensitive for assessing all of the components of daily energy expenditure, except for the cost of voluntary activity under free living conditions, and is therefore the most likely to uncover differences in energy expenditure for weight maintenance induced by chronic CR. As shown in Table 2, 5-11 subjects are sufficient to detect a 10% decrease in absolute or adjusted 24-h energy expenditure. Furthermore, assuming an intra-subject variability of 7.5%, a 15% decrease in total daily energy expenditure can be detected by doubly labeled water with only 11 subjects per group. With 15 subjects enrolled per arm in the study, we feel confident that we will have the necessary power of detecting significant decreases in both sedentary and total daily energy expenditure.

**Secondary outcomes**. While the proposed studies have sufficient power to detect differences for the primary endpoint, because of the novelty and opportunity offered by this study, we also plan to monitor several secondary outcomes of interest in a more descriptive manner. However, the methods and number of subjects may not always be up to the task of uncovering suspected differences.

1. Changes in body composition. We hypothesize that approximately 2/3 of wt. loss during CR will be fat mass, but more (75%) when a combination of CR and increased PA is the cause of similar negative energy balance. Body composition will be measured by DEXA, the new gold standard. Because of the precision and reliability of the method, small differences in changes in fat mass and fat-free mass can be detected.
2. Changes in oxidative stress. At baseline and at different phases of the study, oxidative stress will be measured indirectly by DNA damage, lipid peroxidation (isoprostanes), and protein carbonylation.
3. *Changes in neuroendocrine activities*. The thyroid, somatotropic, and adrenal axes will be measured over 24 hrs. by blood sampling and compared to changes in leptin profile. Activities of the thyroid and somatotropic axes are hypothesized to decrease in response to CR, whereas the adrenal axis will increase. Differences in areas under the curve will be detectable with our number of subjects.
4. *Sympathetic nervous activity* is predicted to decrease in response to CR (spectral analysis of heart rate and urinary excretion of catecholamines).
5. *Changes in cardiovascular disease risk factors and insulin sensitivity/secretion.* We hypothesize that both CVD factors and insulin sensitivity will improve in a similar manner in the groups subjected to CR alone or a combination of CR+PA. Insulin secretion is not expected to change.
6. *Changes in* *tissue gene expression*. We will measure these changes in muscle and adipose tissues by quantitative RT-PCR. The aim of this endpoint is to test the hypotheses that CR alters the pattern of gene expression in adipose tissue and skeletal muscle such that: a) oxidative stress is reduced; b) energy is conserved, and; c) “ancient” genes associated with longevity are regulated in a fashion consistent with involvement in longevity from animal data.
7. *Changes in quality of life*.We hypothesize that subjects enrolled in these studies of CR or CR+PA will improve their quality of life because of weight loss. However, subjects enrolled in the CR+PA group will have a better quality of life than those in the CR alone group.

| **METHODS AND PROCEDURES.** |
| --- |

###### **Psychological Assessment measures**

Most of the questionnaires described below are attached in an Appendix.

Psychiatric Disorders at Screening

Structured Clinical Interview for Diagnosis of DSM-IV Axis I disorders (SCID)113. The SCID is an interview assessing all of the primary psychiatric disorders as defined by DSM-IV (Amer Psych Ass, 1994114). A trained fellow in psychology will conduct the interview, and [name] will make diagnoses (Appendix V).

Assessment of Eating Disorder Symptoms

Safety of the CR procedures is one of the crucial questions to be addressed in this research project. Voluntary dietary restriction is considered to be a common precursor to the development of eating disorders 129, though there is considerable debate about the significance of this risk when advising overweight adults 130. To objectively assess eating disorder symptoms throughout the study, 3 measures were selected, together providing a comprehensive approach for measuring the safety of CR, as it pertains to eating disorders.

Body Shape Questionnaire *(*BSQ)131. The BSQ will be used to measure concern with body size and shape, a common feature of sub-threshold eating disorders. The questions of the BSQ are not face valid as indices of eating disorders, which makes it a good screening measure. The BSQ has been found to be one measure that can predict the onset of eating disorder symptoms 132. Participants who score greater than 100 will be excluded at baseline. Participants who score greater than 120 at any assessment point of the experiment will be considered for termination from the study (Appendix V).

Interview for Diagnosis of Eating Disorders, version 4 (IDED-IV)115. The IDED-IV will be used to screen for the presence of eating disorders at baseline, an exclusion criterion for the study. The IDED-IV is the only interview method that has been validated for the diagnosis of anorexia nervosa, bulimia nervosa, and binge eating disorder. The IDED-IV will also be administered at 6-mo intervals to assess for the development ofeating disorders. Persons who report 4 of the 8 combined symptoms of anorexia or bulimia nervosa will be excluded.

Multiaxial Assessment of Eating Disorder Symptoms(MAEDS)133. The MAEDS is a self-report inventory that measures the six symptom domains related to eating disorders: binge eating, restrictive eating, purgative behavior, fear of fatness, avoidance of forbidden foods, and depression. Scores on all scales are standardized using t-scores. Participants who score greater than a t-score of 70 (two standard deviations above means for a normative sample) on 3 or more scales will be excluded at any phase of the experiment.

Three Factor Eating Questionnaire (TFEQ): TFEQ is a 56-item measure that assesses three aspects of eating and hunger. The Restraint scale measures current dietary restriction. The Disinhibition scale measures the extent to which the participant eats in response to external (e.g., emotional, social) triggers. The Perceived Hunger scale provides a global level of hunger and is correlated with the Disinhibition scale.

Revised Restraint Scale (RS). The RS is a 10-item questionnaire designed to assess eating patterns of eaters who are currently attempting to restrict their dietary intake. The scale is reported to have adequate reliability and validity among normal weight subjects, accurately predicting different eating patterns. Scores less than 15 defined unrestrained eating; scores 15 and greater defined restrained eating.

Dieting Questions. Current dieting is defined as a current effort to restrict caloric intake to lose weight. Three questions have been validated as indicators of current dieting, with a high level of internal consistency (alpha = .85).

Dutch Eating Behavior Questionnaire (DEBQ). The DEBQ is a 33-item measure designed to assess current dietary restraint and the tendency to overeat in response to negative emotions or external cues. Normative data are available according to gender and weight status.

# Assessment of Quality of Life, Mood, and Psychopathology

Measures of quality of life, mood, and psychiatric symptoms will be administered at baseline and at each assessment point.

General Quality of Life. The Satisfaction with Life Scale will be used to measure overall quality of life. This 5 item scale has been found to be a reliable and valid indicator of quality of life 134. It will be administered at baseline and at 6-mo. intervals to assess changes in quality of life. This brief measure has been used in many studies with many different populations 135. Also the RAND 36 item Health Survey (SF-36)136 will be administered to assess eight health outcomes related to CR, e.g., energy/fatigue, emotional well being, and general health perceptions. General Health indicators, e.g., somatic symptoms and social dysfunction, will be measured using the 28 item General Health Questionnaire (GHQ)137.

Depression. Symptoms of depression will be measured using the Beck Depression Inventory II (BDI-II)138. The BDI-II can be used to assess current levels of depression (past two wks.)(Appendix V).

Psychopathology. General psychopathology will be measured using the Symptom Checklist 90 (SCL-90)139. The SCL-90 measures 9 psychiatric symptom domains and 3 general indices of psychopathology. It can be used to measure current psychopathology (Appendix V).

**Assessment of Cognitive Function**

At each assessment period, cognitive functions (memory, attention, and concentration) will be objectively evaluated using 4 tests selected to measure relatively subtle changes in cognitive functions possibly associated with CR.

Auditory Consonant Trigrams (ACT)140. The ACT is a sensitive measure of attention and memory to auditory verbal stimuli. It has been validated as a measure of prefrontal lobe functioning 141.

Conners Computerized Continuous Performance Test (CCCPT)142. The CCCPT is a computerized reaction time test for visual stimuli. It is very sensitive to changes related to attention and concentration.

Rey Auditory Verbal Learning Test (RAVLT)143. This verbal learning test uses a fixed order word list format. Immediate and delayed recalls are measured. Also there is a recognition memory task in the RAVLT. There are alternate forms for the test, which allows for use in a longitudinal study.

Benton Visual Retention Test (BVRT)144. The BVRT is a memory test that has alternate forms and can be used in longitudinal studies such as the proposed study. The BVRT uses nonverbal visual stimuli to assess immediate and delayed recall.

At baseline and at different time periods (see Figure 1), tests will be conducted on our inpatient metabolic ward (4.5 day admission) using the scheme presented in Figure 2 and the following methods.

**Figure 2:** Testing block (4.5d admission at PBRC from days 14-18)

7am

9am

11am

1pm

3pm

5pm

7pm

9pm

7am

**Day 14**

**Day 15**

**Day 16**

**Day 17**

**Day 18**

**Biopsy**

**EKG**

**+ meal**

**Psychological Testing**

**Strength test**

**O2**

**Efficiency**

**TRH stimulation Test**

**NE Test**

**(**

**DEXA**

Admission, Day 13, 5pm

**cont**

**.)**

**NE Testing [**

**Cortisol**

**(8am-5pm), 24h**

**leptin**

**(8am-8am), 12h GH (9pm-8am), Fasting Blood (8am)**

**23h metabolic chamber with urine collection, core temp and VAS**

**CT scan, MRS**

FSIGT

**RMR**

The measure of energy expenditure by doubly labeled water will be performed from days 1-14. The VO2 max, DEXA, fat selection (MSSP) and brachial artery tests will also be performed during that period as an outpatient. The order of tests in this figure is representative only. Test order may change if the availability of equipment changes.

**Body composition and bone mineral density**.

**DEXA** scans will be performed using a new Hologics QDR 4500A whole-body scanner. The protocol requires that subjects lie on a table wearing a hospital gown and no metal containing objects, while the scanner emitting low energy X-rays, and a detector passes along the body. The scan takes less than 4 min. and the radiation dose is less than 1 mrem, equal to about 12-h of background radiation. The scans are analyzed with the latest software QDR for Windows V11.1. Using our old instrument (QDR 2000), coefficients of variation (CV) for body composition measurements of lean mass, fat mass and percentage of body fat were 0.8%, 1.6%, and 1.7%, respectively. We will also use the DEXA data to estimate muscle mass using a method developed by [name] group 145.

Bone mineral density of the hip and proximal femur will be measured on the same scanner in a matter of mins. Subjects lie supine and motionless while the DEXA scanner moves along the length of the subject’s left femur and lasts approximately 2 min. for a 6-inch length. The hip regions of interest are the femoral neck, ward’s triangle, greater *trochanter,* and inter-trochanter region. Area, BMC, and BMD are all measured. For the most part, the analysis is automated, with Ward’s triangle being automatically located by the system, because this is the area of initial bone loss in the femoral neck. There is a reference database for comparing BMD vs. age. Potential changes with intervention will be assessed.

##### Computed tomography

Abdomen for fat distribution. A single cross-sectional, 1cm width, scan is obtained centered at L2-L3, using 170mA, a scanning time of 1 s, and a 512 x 512 matrix (GE Light Speed, General Electric, Milwaukee, WI). Using commercially available software, areas of bone, adipose tissue and skeletal muscle are measured electronically by selecting regions of interest defined by attenuation values: ~200 HU (Hounsfield units) for bone, ‑30 to ‑190 HU for adipose tissue, and 0-100 HU for muscle. Mean muscle attenuation is determined from all pixels within this range 146-148.

Thigh and calf for muscle lipid infiltration. A single 1-cm thickness cross-sectional scan will be obtained of both the mid-thigh and mid-calf will be obtained by computed tomography (GE High Speed, General Electric, Milwaukee, WI). The 3-second scan will be performed at 120 kV (peak), 100 mA, to measure thigh lean tissue and adipose tissue cross-sectional area, composition (lean tissue) and distribution (adipose tissue). Subjects will be scanned while supine. The field of view is 32 cm and the matrix is 512 x 512 pixels. A range of attenuation values will define regions of interest for measurement of tissue areas. Thigh adipose tissue is electronically measured by using commercially available CT software (GE Medical Systems, Milwaukee, WI), with the region of interest window set to attenuation values of -200 to -1 Hounsfield units (HU).

To determine adipose tissue distribution, the fascia lata will be identified and outlined by manual cursor and regions of interest, set to the attenuation range for adipose tissue, will be used to measure the cross-sectional area of adipose tissue above and beneath the fascia lata.

Spectral Magnetic Resonance Procedure (MRS).A magnetic resonance scan will be performed at the Neuromedical Imaging Center on [name] in Baton Rouge. During the sMR experiments, subjects will be asked to lie supine on the patient table of the 1.5 magnet for approximately 45 min.Measurements will be obtained from the calf with the subject's leg positioned inside a radio frequent (RF) 1H coil. Because the degree of knee extension and the angle of foot rotation can affect the quality of the spectra (i.e the amount of splitting between the IMCL and EMCL peaks), the actual positioning of the lower leg will be determined. Foam pads and pillows will be used to ensure the subject will rest comfortably during the testing. The subjects will be informed that the imaging scans will produce loud “knocking” noises and a headset with music will be provided to mask and minimize this noise.

**Exercise monitoring and VO2max**

Exercise monitoring. Subjects will be instructed to maintain their PA and exercise habits during the 6 months. of intervention unless they are randomized to the CR+PA arm. In this arm, subjects will be instructed to comply with their almost daily exercise prescription. PA levels will be monitored for one week each month by providing each subject with their own portable heart rate monitor and accelerometer and regularly (twice weekly) downloading 24-h data from these free-living monitors. Uni-axial accelerometers will be used to monitor free-living PA 149,150. The Stanford 7 day physical activity recall will also be administered once per month to all subjects to monitor any change in PA levels.

In addition, free-living 24-h energy expenditure (doubly labeled water) will be measured periodically throughout the study and will serve as an additional insurance. Subjects will be blinded as to when the doubly labeled water tests will be performed. This will be achieved by “dosing” the subjects with either tap water or doubly labeled water every 2 weeks. The participants will also provide urine samples each week. In Phase 1 of CALERIE actual dosing with labeled water will occur twice at baseline, at one month and at 3 and 6 months. Subjects who appear to have changed their exercise and/or PA patterns (compared to baseline) will be interviewed and the situation corrected. Subjects who fail to comply with these constraints will be further counseled and compliance strategies will be discussed.

Whole-body maximal aerobic power (VO2max) and strength VO2max will be measured by a progressive treadmill test to exhaustion using standardized procedures. Testing will be performed in the morning after an overnight fast, using a modified Bruce protocol, which has been used successfully in sedentary and endurance-trained subjects at a variety of fitness levels 151,152. During the test, O2 consumption and CO2 production will be measured continuously by indirect calorimetry and heart rate will be recorded. A physician will be present for measures in subjects who are older than 45 or have at least one of the risk factors as described by the ACSM guidelines for exercise testing and prescription 153. These subjects will be monitored using a 12-lead EKG.

Muscle strength and endurance will be measured via isokinetic testing on a Cybex machine during knee extension and flexion. Isokinetic testing allows for measurement of force velocity or power velocity curves as well as peak force and peak power. Unlike other methods of measuring strength, isokinetic testing is quick and less likely to cause injury in subjects not used to performing this type of testing. Before isokinetic testing, subjects will have an introductory trial to the procedure for familiarization with the task. The procedure involves an initial test of 3 repetitions at 60 degrees/sec. to measure peak force and power followed by a test to fatigue at 180 degrees/sec.

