**Figure 1**

; 6-

mo

Experimental Design

Time

0

1

2

3

4

5

6

mo

.

Control

25% CR

12.5%CR +

12.5% PA

LCD 800 kcal/d

-15% wt,

CR alone

Randomization

Feeding at PBRC

Green blocks denote metabolic test periods at baseline, 3 and 6 month periods (doubly labeled water plus 5-day inpatient stay (3 weeks total). Yellow blocks denote doubly labeled water measurements only (2 weeks).

This study is to test the feasibility and compliance to a 25% CR diet using several creative strategies, and to pilot and test several of the methods for a subsequent longer calorie restriction study. These include methods for assessing PA under free-living conditions, refinement of the assessments of the neuroendocrine axes, validation of the measure used to assess DNA oxidative stress, and final selection of the genes for tissue mRNA measurements. Because of the tight control of diet and exercise program, it will be impossible to blind all study personnel to the intervention assignment. However, most of the personnel performing the assessment measures (for ex. lab work, DEXA, energy expenditure etc.) will be blinded.

It is anticipated that compliance will be difficult for the volunteers and difficult to assess. Because of this, and in an attempt to improve the ease of compliance and to encourage it, all the volunteers will receive their meals at the Center for the initial 3.5 mos., and during the metabolic testing days. Compliance, however, will still be difficult to assess, since the measured parameters, including body weight, body composition, energy expenditure, dietary records, etc. are insufficiently precise or accurate to provide real-time objective information about it. Therefore, we have included a “weight clamped” group of subjects who have lost 15% of body weight by medically supervised LCD. This will allow the outcomes of interest to be assessed in a group of volunteers who will precisely maintain a new energy balance at an intake predicted to be 20-25% below their baseline energy requirements after rapid wt. loss (15%).

Screening of Subjects, Diet, Exercise Regimen and Behavioral intervention

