The Pennington Metabolic Kitchen staff will prepare all food consumed in the chamber. At baseline, the energy content will be estimated according to a previously developed equation and adjusted during the day on the basis of the energy expenditure of the first 7 hrs. of measurement 156. After the baseline recording, energy content of the food for the subsequent chamber measures will be calculated as 100%, 87.5%, or 75% of baseline 24-h measured energy expenditure, according to the study arm. 24-h urine will be collected for norepinephrine and cortisol excretion rates determinations. During each stay in the chamber, subjects will be asked to fill visual analogue scale (VAS) to measure hunger, satiety, fullness and desire to eat during the course of the day. These VAS tools, first developed by Blundell have been fully validated 157 and used in association with plasma leptin changes in relation to daily changes in hunger and satiety 158. Core temp. will be measured and recorded every 5-min. during the 24 hrs. of energy expenditure measurements in the chamber. At 7:00 AM the volunteers will swallow a 10 x 20-mm silicone coated radio-capsule (Human Technologies, Inc St Petersburg, FL) and will be fitted with a bandoleer type antenna system, connected to a portable monitor that records core temp.

Doubly-labeled Water*.* On Day 0, a fasting baseline urine sample is collected, a metabolic weight taken and a DEXA scan performed. Following this, subjects will drink from a stock solution with 0.22g/kg total body water (TBW) of H218O (Cambridge Isotopes, Cambridge, MA) and 0.115 g/kg TBW of 2H2O (Isotec Inc., Miamisburg, OH or Cambridge Isotopes, Cambridge, MA), followed by a 100-200ml of tap water used to rinse the dose container. Following 2 voids, two consecutive urine samples are collected (at 4 and 6.5 hours after dosing). For the next 14 days after dosing urine samples are collected each morning after breakfast. On Day14, a metabolic weight and DEXA scan is repeated. Additional DLW measurements may be used to monitor compliance periodically throughout the study (at 1 month for Phase 1). Urine samples will be collected on days 0, 7 and 14 only for these additional measurements.

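### The stated blinding to labeled-water timing cannot hold at months 3 and 6, the two post-baseline doses that supply the free-living part of the primary endpoint

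*Protocol*

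**What the plan says.** Under Exercise monitoring and VO2max, the protocol states without limit that "Subjects will be blinded as to when the doubly labeled water tests will be performed". The device is to dose "the subjects with either tap water or doubly labeled water every 2 weeks", and "The participants will also provide urine samples each week". The same paragraph says that "actual dosing with labeled water will occur twice at baseline, at one month and at 3 and 6 months".

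The Doubly-labeled Water paragraph under Energy expenditure sets out the full procedure. On day 0, "a fasting baseline urine sample is collected, a metabolic weight taken and a DEXA scan performed". Two timed urines follow at 4 and 6.5 hours. Then: "For the next 14 days after dosing urine samples are collected each morning after breakfast". Weight and DEXA are repeated on day 14. A lighter version applies to extra compliance measurements, of which month 1 is the one named: "Urine samples will be collected on days 0, 7 and 14 only for these additional measurements".

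The legend of Figure 1 ties the full procedure to the main visits: "Green blocks denote metabolic test periods at baseline, 3 and 6 month periods (doubly labeled water plus 5-day inpatient stay (3 weeks total". The text under Figure 2 puts the labeled-water period on days 1 to 14 of that block, with outpatient tests in the same fortnight. Figure 2 has the admission starting on the evening of day 13.

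The Outcome measures section names free-living expenditure as one of three components of the primary endpoint, with resting and sedentary (chamber) expenditure as the others.

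**The concern.** A sham dose hides a test only if everything around the dose looks the same. Here the sham covers the drink and a weekly urine, while the procedure at months 3 and 6 is far heavier and belongs to a test block that participants have already been through at baseline. They can be expected to know which fortnight is being measured.

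That matters for the free-living component. The protocol also uses labeled water as a check on activity and compliance, and derives an estimate of energy intake from it. A participant who recognizes the window may complete every exercise session, or keep more closely to the diet, during those two weeks only.

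Any exercise shift would probably differ by arm, because CR+PA has a prescription to fulfil and the other arms are told to keep their habits. Extra sessions in the window would raise measured free-living expenditure in CR+PA. That is the direction of the protocol's own hypothesis that adding activity blunts the metabolic effects of restriction.

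**Working it through.** **Inputs.** The dosing plan and sham scheme come from Exercise monitoring and VO2max. The cycle procedures come from the Doubly-labeled Water paragraph. The test blocks come from Figure 1, Figure 2 and the text beneath. The exercise prescription comes from the Exercise section. The protocol gives no figure of its own for how well the blind works, so there is none to reproduce.

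**Step 1: the cycles side by side.**

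| Feature | Tap-water cycle | Month-1 labeled cycle | Month-3 and month-6 labeled cycles |
| --- | --- | --- | --- |
| Urines | weekly | days 0, 7 and 14 | fasting on day 0, two timed after the dose, 14 mornings |
| DEXA | none described | not stated | days 0 and 14 |
| Attached test block | none described | none described | three-week block with outpatient tests and admission |

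Only the month-1 urine schedule matches the weekly scheme.

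**Step 2: urines per two-week cycle.** Full labeled cycle: 1 + 2 + 14 = 17. Weekly scheme, assuming the urines fall on days 0, 7 and 14: 3. The daily collection alone conflicts with the weekly rule, whatever is assumed about DEXA.

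**Step 3: how many labeled doses can be masked.** Labeled doses: 2 at baseline + 1 at month 1 + 1 at month 3 + 1 at month 6 = 5. Baseline testing ends before randomization and no sham cycle is described there, so the relevant count is 5 − 2 = 3. Month 1 can be masked: 1 of 3. Of the two post-baseline doses in the main test blocks, 0 of 2 can be masked.

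**Step 4: illustration of a possible shift in CR+PA.** The prescription is 12.5% of daily need, spread over five sessions a week. The need of 2500 kcal/d and the usual session counts outside the window are assumptions.

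- Cost per session: 0.125 × 2500 × 7 / 5 = 437.5 kcal.
- Five sessions a week in the window instead of a usual four: 2 extra in 14 days, 2 × 437.5 / 14 = 62.5 kcal/d, and 62.5 / 2500 = 2.5%.
- Five instead of three: 4 extra in 14 days, 4 × 437.5 / 14 = 125 kcal/d, and 125 / 2500 = 5%.

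Three is the number of weekly sessions required at the Center after the training phase, so the 5% case means that every optional session is skipped outside the window and none inside it. For scale, Table 2 assumes a 7.5% within-subject CV for labeled water, and the text under Outcome measures aims at a 15% decrease.

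**The case against.** The strongest reply is that the blinding sentence stands in a passage on monitoring activity and serves a compliance check. For the month-1 dose, the measurement with that stated purpose, the urine schedule fits the sham and the blind can work. This is fair for month 1. But the sentence is not limited to month 1, and the same paragraph lists months 3 and 6 among the labeled doses.

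Second, the protocol does not say that tap-water cycles lack DEXA scans or timed post-dose urines. That is true; it is read from silence. The conflict between weekly and daily urines is in the text and is enough by itself.

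Third, the admission starts only as the labeled fortnight ends, so it cannot signal the window while most of it runs. This also stands. The admission reveals timing only through the known block schedule.

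Fourth, existing controls limit gaming. Meals come from the Center up to month 3, which leaves little room to change intake only in that window. CR+PA participants do three sessions a week at the Center, with logs and heart-rate data. These controls reduce the likely shift. They are weaker at month 6, when diets are self-selected, and for the two optional sessions.

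A reader might also infer that the whole primary endpoint is compromised. The documents do not support this: the ventilated-hood and chamber measurements do not depend on this blind, and the power analysis rests on the chamber.

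**Conclusion.** The point holds for the free-living component. As written, the blind can hold for 1 of 3 post-baseline labeled doses and for neither the month-3 nor the month-6 dose. This rests on the conflict between weekly and daily urines, supported by the DEXA scans and by a test block known from baseline. Even month 1 rests on the assumption that its cycle omits the DEXA scans, which the text does not settle.

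The size of any change in behaviour is unknown. The 2.5% to 5% range depends on an assumed need and assumed session counts, and applies to one arm. A reader might take it as an estimate of bias, but nothing in the protocol supports that. A reader might also infer that the later values are going to be reported as blinded. The protocol does not say so; it states the blinding without limit, and that leaves the description open.

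**What to change.** 1. Reconcile Exercise monitoring and VO2max with the Doubly-labeled Water paragraph. Limit the blinding statement to the month-1 type of measurement, say whether that cycle omits DEXA, and do not describe the month-3 and month-6 free-living values as blinded.
2. The protocol already plans one week of accelerometer and heart-rate monitoring each month. Place the month-3 and month-6 weeks inside the labeled fortnights. Compare them, together with the exercise logs in CR+PA, with the monitored weeks of months 2, 4 and 5. In CR+PA the month-2 week should fall after the six-week build-up in Table 1. Report the difference between inside and outside the window by arm, beside the free-living result.

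Matching the urine schedules of tap-water and labeled cycles is a tempting alternative, but it would not restore the blind: DEXA and the test block would still reveal months 3 and 6.

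The cost is a wording change, a small scheduling constraint and one descriptive table. The monitors are visible to participants, so the comparison may understate the shift.
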